#### 2.11.4. Falls during Baseline and 12-Week Follow-Up

We will use the McNemar test to compare the numbers of non-fallers and fallers during the baseline period and the 12-week follow-up period.

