#### 2.7.5. Falls

We defined a fall as an event that results in a person coming to rest inadvertently on the ground, floor, or other lower level [46]. We will use a fall calendar during the baseline period and the 12-week follow-up period. Falls are logged daily by the participant or the involved professional caregiver by putting a green sticker (no fall) or a red sticker (fall) on the calendar. If a participant falls multiple times during the day, the number of falls will be written down. The professional caregiver will check the calendar for completeness. For each period, we will classify participants as a non-faller or a faller (≥1 fall).

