#### 2.11.2. Effect of PRET Programme (Post-Intervention)

We will use two-level hierarchical linear and logistic regression models to investigate the effect of the PRET programme at the end of the intervention period (T3). The first level consists of the repeated measurements nested within a participant; the second level consists of the clustering of participants by the trainer delivering the PRET programme. We will use the likelihood ratio test (correcting for the boundary) to assess the necessity for random coefficients in the regression model. Statistical analyses will be performed with R-statistics (R Foundation for Statistical Computing, Vienna, Austria) and we will use the package Linear and Nonlinear Mixed Effects Models (nmle) [50]. A two-tailed significance level of 0.05 will be used for all tests.

The variables for the PRET programme will be coded as 0 (baseline period at T0, T1, and T2) or 1 (intervention period T3). To check the assumption of stable baseline measurements, we will investigate the effect of time on each outcome variable assessed during the baseline period. Time varying variables (changes in sport activities and medication use related to CVRF) will be included as covariates in all models.

We will use the data from all participants who started the study. We will also analyse the effect of the intervention for participants who completed the intervention as planned.

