### 2.12. Sample Size Calculation

We calculated the sample size for the outcome HbA1c using simulated data and repeated the simulation a 1000-times in a hierarchical way. To determine the effect of the trainers we used the outcome of our pilot study [25] where we found a variation of 30% for the clustering of participants by the trainer who delivered the PRET programme. The type 1 error (alpha) was set at 0.05 and power was set at 80%. We used an effect size (mean change in %HbA1c = −0.55, SD = 0.47) derived from a study that examined the effect of high intensity resistance training in adults with diabetes mellitus type 2 [10]. This resulted in a sample of 35 participants needed for this study. In our pilot study, 58% of the participants completed the PRET programme successfully at intended intensity [25]. Therefore, we inflate the number of participants by 42% and aim to enrol 61 participants in this study.

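### Daily fall counts are collected but only faller status is tested; adding a paired analysis of the fall rate would use the data better

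*Protocol article*

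**What the plan says.** Section 2.7.5 of the protocol article uses a fall calendar in the 12-week baseline period and again in the 12-week follow-up period. Each day gets a green sticker (no fall) or a red one (fall), and "If a participant falls multiple times during the day, the number of falls will be written down". The professional caregiver checks that the calendar is complete.

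The same section then reduces the record to two classes: "For each period, we will classify participants as a non-faller or a faller (≥1 fall", closing the bracket there. Section 2.11.4 names one analysis: "We will use the McNemar test to compare the numbers of non-fallers and fallers" in the two windows. The article gives the counts no other use.

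Section 2.11.2 sets the error level: "A two-tailed significance level of 0.05 will be used for all tests". Section 2.12 sizes the study on HbA1c alone. The article gives no fall rate, expected reduction or power for falls, which are a named secondary outcome.

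**The concern.** The reduction to two classes is a stated choice, not a detail left to another document. McNemar uses only participants whose class changes. Someone who falls six times at baseline and once at follow-up is a faller both times and contributes nothing, although this is the kind of change a strength programme might produce. The Discussion hopes that training will reduce falls. A reduction concentrated in repeat fallers could therefore be largely missed.

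A second, smaller point concerns the outcome itself. The chance of at least one fall rises with the number of days observed, and the faller class has no denominator. A rate per day logged has one.

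The number enrolled is fixed by HbA1c, so the choice of analysis is the main remaining influence on what the falls data can show.

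**Working it through.** **Sample available.** The enrolment target reproduces: 35 / 0.58 = 60.3, rounded up to 61. The 35 comes from the HbA1c simulation and says nothing about falls. I use N = 61 below.

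**Inputs from the article:** two equal planned windows of 12 weeks; two-sided alpha 0.05; faller means at least one fall.

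**Assumed inputs (not in the article):** mean falls per 12 weeks at baseline from 0.3 to 2.0; true rate ratio 0.5; Poisson counts with gamma variation between persons (dispersion = 1/shape).

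**Tests compared.**
- McNemar, asymptotic: (b − c)² / (b + c) against 3.84, where b and c count the participants who change class in each direction. The exact version uses the binomial distribution. The article does not say which is meant.
- Sign-flip: d = baseline falls − follow-up falls for each person and T = Σd. The sign of each d is flipped at random 999 times, and p is the share of |T*| at least as large as |T|.
- Count statistic: z = Σd / √Σd², compared with 1.96. With equal windows this is the large-sample form of the sign-flip test.

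The participant going from six falls to one adds 0 to b and c, but d = 5 to the count tests.

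**A. Stable personal rates, sign-flip test** (1,500 runs; simulation error at most about 1.96 × √(0.25/1500) = 2.5 points)

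| Mean falls | Gamma shape | McNemar (asymptotic) | Sign-flip | Difference (points) |
|---|---|---|---|---|
| 0.3 | 1 | 34% | 33% | −1 |
| 0.45 | 1 | 43% | 48% | 5 |
| 0.6 | 0.5 | 43% | 59% | 16 |
| 0.8 | 0.5 | 45% | 73% | 28 |
| 1.2 | 0.3 | 39% | 88% | 49 |

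Sign-flip type I error was 3–5%. With weak overdispersion the difference was about 2 points (52.5% vs 54%).

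**B. Stable personal rates, count statistic, dispersion 1**

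| Mean falls | McNemar exact | McNemar asymptotic | Count statistic |
|---|---|---|---|
| 0.3 | 25% | 33% | 39% |
| 0.6 | 42% | 51% | 68% |
| 1.0 | 49% | 59% | 86% |
| 2.0 | 54% | 65% | 99% |

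The count statistic's type I error at N = 61 was about 5%. At mean 0.3 its apparent gain of 6 points disappears with the sign-flip test in table A, so no gain should be claimed for rare falls.

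**C. Personal rates that also vary between windows** (between-person dispersion 1; asymptotic McNemar vs count statistic)

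| Mean falls | Window dispersion 0.5 | Window dispersion 1 | Window dispersion 2 |
|---|---|---|---|
| 0.3 | 27.7% vs 31.8% | 23.9% vs 27.7% | 18.9% vs 21.1% |
| 0.6 | 40.1% vs 51.0% | 33.3% vs 41.9% | 24.6% vs 28.9% |
| 1.0 | 47.1% vs 64.6% | 38.0% vs 49.2% | 26.2% vs 31.7% |

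Differences run from 21.1 − 18.9 = 2.2 points to 64.6 − 47.1 = 17.5 points, and are smallest where the variation between windows is strongest. The sign-flip test in similar scenarios (window gamma shape 1) gave 30% vs 32% at mean 0.45, 34% vs 38% at 0.6, 29% vs 36% at 0.8 and 27% vs 35% at 1.2.

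**D. Smaller effect.** At rate ratio 0.7 and dispersion 1 with stable rates, asymptotic McNemar vs count statistic was 13% vs 15% at mean 0.3 and 24% vs 67% at mean 2.0.

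**The case against.** **McNemar is a correct test here.** The outcome is paired and binary, and the planned windows are equal. Falls are one of six secondary outcomes, no power is promised for them, and no stated figure is contradicted. This stands: the point is about efficiency, not error.

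**Faller status and fall rate answer different questions.** A few frequent fallers can dominate a rate, and the faller class resists that. This also stands, and it is why McNemar should be kept and not replaced.

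**The power figures rest on assumptions.** A rate ratio of 0.5 is large, and the biggest gains need skewed but perfectly stable personal rates. This stands too. Only the usual direction can be relied on, and for rare falls not even that.

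**A stronger reading that a reader might infer** is that the plan ignores incomplete calendars and so leans towards a benefit if follow-up logging is poorer. The article does not support this. It has a completeness check, and the green stickers distinguish a day without a fall from an unlogged day. It does not say that partial calendars will be scored as they stand, and a rule for them may be in the full protocol. If 30% of participants logged only half the follow-up window, partial calendars were used unadjusted and there were no true effect, type I error would be about 6–13% for asymptotic McNemar and about 4–8% for the exact version. The 30% has no basis in the article. All that can be said is that the faller class carries no exposure term.

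**Conclusion.** The point holds as a low-severity, inexpensive improvement. The article collects daily counts, keeps only faller status and tests only that. The test is valid, but it discards change among repeat fallers and usually gives up power.

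Against asymptotic McNemar, with N = 61 and an assumed rate ratio of 0.5, the gain from a paired count analysis is:
- none at a mean of 0.3 falls per 12 weeks (sign-flip test);
- about 2 to 17.5 points when personal rates also vary between windows;
- about 15 to 50 points when falls are frequent or skewed and personal rates are stable.

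The article gives no fall rate, dispersion or expected reduction, so it cannot be said which case applies. It would be wrong to conclude that the planned test is invalid, or that it is shown to be biased.

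**What to change.** Add to section 2.11.4 that falls per day logged will be compared between the two windows with a two-sided paired sign-flip permutation test, with McNemar on faller status reported beside it. Days logged are the days with a green or red sticker, so the rate supplies the missing exposure term. In the half-logged scenario above, the sign-flip test on exposure-scaled counts kept a type I error of 3–4%.

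A Poisson rate-ratio test with robust standard errors should not be offered on equal terms: it showed 6–8% type I error in simulation under assumptions of this kind.

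The cost is about one sentence and no new data. It is best settled before the follow-up falls data are seen. The drawback is that a few frequent fallers can weigh heavily in the rate; the retained McNemar result shows whether the conclusion depends on them.

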### 2.12. Sample Size Calculation

We calculated the sample size for the outcome HbA1c using simulated data and repeated the simulation a 1000-times in a hierarchical way. To determine the effect of the trainers we used the outcome of our pilot study [25] where we found a variation of 30% for the clustering of participants by the trainer who delivered the PRET programme. The type 1 error (alpha) was set at 0.05 and power was set at 80%. We used an effect size (mean change in %HbA1c = −0.55, SD = 0.47) derived from a study that examined the effect of high intensity resistance training in adults with diabetes mellitus type 2 [10]. This resulted in a sample of 35 participants needed for this study. In our pilot study, 58% of the participants completed the PRET programme successfully at intended intensity [25]. Therefore, we inflate the number of participants by 42% and aim to enrol 61 participants in this study.

## 3. Discussion

In this study we will examine the effects of the PRET programme on CVRF, physical fitness, sarcopenia, activities of daily living, falls, and challenging behaviour in adults with mild to moderate ID. These health issues are highly prevalent in this population [3,15,21,22,23] and non-pharmacological treatment strategies are needed to reduce the impact of these problems on health. If the PRET programme is effective in reducing CVRF, then it may be added as a strategy to existing interventions to reduce cardiovascular risk in adults with ID. Additionally, gaining muscular strength may increase physical fitness levels, reduce sarcopenia, enhance the ability to perform activities in daily life and reduce falls. The programme may have a positive impact on challenging behaviour.

A randomised controlled trial is often considered the gold standard for intervention research and offers the ability to reduce bias due to confounding [51]. We considered a randomised study design; however, randomised controlled trials in people with ID have been challenging. Obtaining informed consent from legal representatives, rather than from eligible participants themselves, often results in small sample sizes and insufficient statistical power [51]. We expect that legal representatives may refuse study participation, as the participant they represent may be allocated to the control group and will not receive the PRET programme. Therefore, we opted for a repeated time series design with one study group. Because of the single group design, we can offer all participants the PRET programme, and all participants may profit from possible health benefits. The use of the repeated measures within each participant will increase the statistical power, and the multilevel regression analyses allow us to adjust for time varying variables such as sport activities and medication use related to CVRF.

Our study design has some limitations. First, we are not able to control for elements of care that we will not measure. This may result in uncontrolled residual confounding. Second, although the measurements used to assess the primary outcomes are objective, the validity of the measurements to assess physical fitness may be influenced by the ability of the participants to follow instructions. However, the results of the physical fitness tests will only be recorded if the trained researcher is convinced that participants understand how to perform the test. Finally, the lack of blinding of the researcher performing the assessments may introduce measurement bias.

A strength of this study is the clinically applicability of the PRET programme. In a pilot study [25] we created a set of feasible resistance exercises for adults with ID (RESID) that we used in the PRET programme. Secondly, we assessed the feasibility of the PRET programme in adults with ID and CVRF [26]. We found that the PRET programme was feasible when close supervision was provided to the participant, with 58% of the participants achieving vigorous training intensity.

Adherence to the PRET programme is important for the internal validity of the study. It may be challenging for adults with ID to complete a 24-week exercise programme because of motivational factors. Based on our experiences from the pilot and feasibility study, we will incorporate several strategies (a progression certificate to track progress, a T-shirt to wear during the training and measurements, and the participant receives a certificate and a medal at the end of the programme) to maximize attendance and motivation of the participants. In addition, the training will be provided by trainers who are experienced in motivating adults with ID when performing physical exercises.

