### 2.2. Study Population, Recruitment, and Inclusion

This study will be conducted within the Healthy Ageing and Intellectual Disability (HA-ID) consortium. The HA-ID consortium is a collaboration between the Chair of Intellectual Disability Medicine of the Erasmus MC, University Medical Center Rotterdam and three care providers in the Netherlands specialised in care for people with ID: Ipse de Bruggen (Zoetermeer), Abrona (Huis ter Heide), and Amarant (Tilburg).

Figure 1 summarises the inclusion and exclusion criteria for this study. Participants must meet the following criteria to be included: (1) being 18 years or older; (2) living in a residential facility or receiving care from one of the participating care providers; (3) diagnosed with mild (IQ = 50–69) or moderate (IQ = 35–49) ID [28]; (4) diagnosed with metabolic syndrome [29], or at least two of the following CVRF: hypertension [30], hypercholesterolemia [4], diabetes mellitus type 2 [31], or obesity [32]. Metabolic syndrome is defined as the presence of any three of the following CVRF: elevated waist circumference, elevated blood pressure, elevated fasting glucose, elevated triglycerides, and low high density lipoprotein cholesterol [29]. Cut-off values for the CVRF are summarised in Table 1. Furthermore, participants must be able to walk independently and able to follow instructions on posture and performance for good execution of the exercises.

We will develop a query to screen medical files for potential participants. Potential participants are screened by a physical therapist for their eligibility and expected adherence to the PRET programme. To identify health issues that make participation in the PRET programme unsafe, the professional caregiver of eligible participants will fill out the Physical Activity Readiness Questionnaire (PAR-Q) [33]. If a positive response to any of the items of the PAR-Q is given, the participant’s physician will do a health check to assure safe participation. Participants who do not obtain medical clearance from their physician or have physical limitations (including neurological and orthopaedic conditions) interfering with participation in the PRET programme will be excluded from the study.

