### 2.4. Intervention

The PRET programme will take 24 weeks and consists of two sessions per week, with at least 48 h between the sessions. The intervention will be led by experienced physiotherapists and physical activity instructors employed by the care providers. All instructors take part in a training prior to the study. In this training, the intervention protocol and exercises will be discussed and practiced ensuring that the intervention is delivered according to the protocol. Every session consists of seven exercises (RESID) to train all large muscle groups [25]. For each muscle group, alternative exercises will be provided for participants who are not able to perform the original exercise with a correct execution. The instructor-participant ratio will be 1 to 1 or 1 to 2.

Table 2 summarises the training parameters of the PRET programme. The programme is in accordance with the ACSM guidelines [11] and characterised by four mesocycles. Each mesocycle consists of six weeks of training. After each mesocycle the training intensity will increase gradually, and within each mesocycle the weights will be adjusted in a way that the intensity remains equal. Training intensity will be measured by the percentage of the heaviest load one can lift for one repetition (% of 1RM) [34]. In the first mesocycle, participants are introduced to the resistance exercises and familiarised to the training protocol. They will learn to perform the exercises safely and with good posture. During mesocycles 2, 3, and 4, the number of repetitions will be gradually decreased while the training intensity will be gradually increased until vigorous intensity is reached in the fourth mesocycle (80% of 1RM). The resting time between sets will depend on the training intensity and varies between 30 s and 2 min.

The instructors will register attendance, training intensity, performed number of sets and repetitions, and the weights used for each exercise in a log. To maximise attendance and motivation, each participant receives a progression certificate to track their progress and a T-shirt to wear during the training and measurements. At completion of the programme, the participant receives a certificate and a medal.

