### 2.7. Secondary Outcomes

#### 2.7.1. Physical Fitness, Muscle Endurance, Muscle Strength, Balance

A trained researcher will use the ID-fitscan to assess physical fitness. The ID-fitscan is a standardised set of performance tests that assesses muscle endurance (30 s chair stand and the five times chair stand), muscle strength (grip strength by hand-held dynamometry), and balance (four balance stances and comfortable walking speed). The set has been found feasible and reliable for adults with ID [36].

For the 30 s chair stand, participants are instructed to stand up and sit down as often as possible, without using their hands. We will record the number of complete stances performed in 30 s. For the five times chair stand, participants are instructed to stand up and sit down five times as fast as possible, without using their hands. We will record the time needed to complete five stances. For both tests, the participant starts sitting in the chair with the feet on the floor and the knees in a 90° angle.

We will use the Jamar dynamometer (Hydraulic, JAMAR, Sammons Preston Rolyan, Nottinghamshire, UK) to measure grip strength. Grip strength is tested in a seated position with the shoulder in 0° flexion and the elbow in 90° flexion. The participant is asked to squeeze the dynamometer with maximum force three times, with one minute rest in between. Both hands will be tested. The maximum produced force of the six attempts (kg) is the final test score.

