### 2.10. Procedures

Figure 1 shows a schematic representation of the study procedures. Participant characteristics will be collected at T0. During the 12-week baseline period, measurements for the primary and secondary outcomes will take place at six-week intervals (T0, T1, and T2). A minimum of three measurements is needed to establish a valid baseline and to filter out the natural variability that may exist in these parameters without applying any intervention [49]. We will record changes in sport activities and medication use related to CVRF. The falls will be tracked continuously throughout the 12-week baseline period.

After the baseline period, the intervention period starts for a duration of 24 weeks. We will record changes in sport activities and medication use related to CVRF. At the end of the intervention period all measurements for the primary and secondary outcomes will be repeated (T3).

The follow-up period will last 12 weeks. Directly post-intervention, we will ask all participants to fill out a questionnaire about their experiences with the PRET programme. We plan interviews with participants and their trainers who want to continue the PRET programme and evaluate facilitators and barriers for successful exercise in their daily life. At the end of the follow-up period all measurements for the primary and secondary outcomes will be repeated (T4). Falls will be tracked continuously throughout the follow-up period. Participants who drop out prematurely from the intervention, will be invited for the measurements at T3 and T4.

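### The recording rule for fitness tests lets an unblinded researcher decide which results exist, and it may select differently at T0–T2 and at T3

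*Protocol article*

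**What the plan says.** The Discussion concedes that "the validity of the measurements to assess physical fitness may be influenced by the ability of the participants to follow instructions". It answers this with one rule: "the results of the physical fitness tests will only be recorded if the trained researcher is convinced that participants understand how to perform the test". The next sentence adds that "the lack of blinding of the researcher performing the assessments may introduce measurement bias".

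Four other places bear on the rule:

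- **Section 2.11.2** defines the comparison. The programme variable is "coded as 0 (baseline period at T0, T1, and T2) or 1 (intervention period T3". Section 2.1 confirms a single study group whose baseline measurements serve as the control.
- **Section 2.11.2** also checks baseline stability, by testing for an effect of time during the baseline period.
- **Section 2.4** describes what participants are taught in the first mesocycle: "They will learn to perform the exercises safely and with good posture".
- **Section 2.7.2 and Table 3** use the chair stand and grip strength, with muscle mass, to classify sarcopenia. Gait speed is added for the severe form.

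**The concern.** The rule is offered as a protection of validity, but it is also a selection rule. It is applied afresh at each visit by someone who knows whether the visit falls before or after PRET. The article treats the missing blinding as a measurement problem only. It does not note that the same person decides whether a measurement enters the data at all.

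In a randomised comparison, such a rule might act alike in both arms. Here the before–after contrast is the only comparison, so any shift in what is kept between T0–T2 and T3 goes into the estimated effect. The baseline stability check cannot reveal a shift that occurs at T3. No later analysis can repair the loss, because the unrecorded results do not exist.

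A shift between phases is plausible. T3 comes after three earlier test rounds and 24 weeks of supervised exercise twice a week. If a weak performance is sometimes read as a failure to understand, the judgement also depends on the score.

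**Working it through.** **Inputs from the article.** Target enrolment is 61, which reproduces from Section 2.12: 35 / 0.58 = 60.3, rounded up to 61. There are four visits (T0, T1, T2 coded 0; T3 coded 1) and a two-sided alpha of 0.05. The article gives no share of fitness tests left unrecorded, and no mean or SD for any fitness test.

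**Assumptions, not in the article.** The outcome is the 30 s chair stand with mean 10. The between-person SD is 3.2 and the within-person SD 2.4, so the total SD is √(3.2² + 2.4²) = √16 = 4 and the within-person correlation is 10.24/16 = 0.64. The true PRET effect is zero. The model has a random intercept.

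**Check 1: recording depends on the score.** Results below the 25th percentile are dropped with a probability that depends on phase. A probability of 0.4 removes 0.4 × 25% = 10% of that phase's data. There were 1,500 runs per row; the Monte Carlo SE of the bias is about 0.01 stands.

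| Drop probability, T0–T2 / T3 | Bias (stands) | Bias / 4 (SD) | False-positive rate |
|---|---|---|---|
| 0.2 / 0.2 | −0.01 | about 0 | 5% |
| 0 / 0.2 | +0.11 | +0.03 | 6% |
| 0.4 / 0.2 | −0.14 | −0.035 | 9% |
| 0 / 0.4 | +0.26 | +0.065 | 11% |
| 0.4 / 0 | −0.27 | −0.07 | 13% |
| 0.2 / 0.6 | +0.30 | +0.075 | 12% |

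More dropping at baseline hides a gain; more dropping at T3 creates one.

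**Check 2: recording depends on understanding.** Total SD is 1, the within-person correlation 0.7, with 400 runs and a Monte Carlo SE of 0.004 to 0.005. Understanding is either unrelated to fitness, or correlated 0.5 with the person's fitness level or with the current result.

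| Recorded, T0–T2 / T3 | Bias, unrelated (SD) | Bias, correlated 0.5 (SD) |
|---|---|---|
| 90% / 90% | +0.001 | −0.003 to −0.007 |
| 95% / 98% | −0.002 | −0.010 to −0.016 |
| 90% / 97% | −0.003 | −0.013 to −0.025 |
| 80% / 95% | +0.009 | −0.033 to −0.057 |
| 70% / 95% | −0.001 | −0.059 to −0.083 |

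If more participants are judged to understand at T3, weaker performers enter only then, and PRET looks slightly worse than it is.

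**Reading the two together.** Bias needs two conditions at once: recording rates that differ by phase, and recording that is related to performance. If either is absent, the bias is essentially nil.

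**Check 3: would analysing all attempts be safer?** Assume that a test that is not understood costs 3 stands. With 90% understanding before and 97% after, analysing every attempt gives a bias of about +0.21 stands and about 10% false positives. With 80% and 95%, it gives about +0.44 stands and about 26%. Better understanding is then counted as better fitness.

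**The case against.** The strongest reply is that the article points to few unrecorded tests and a stable rate. Participants must already be "able to follow instructions on posture and performance for good execution of the exercises" at entry. Of the test set the article says "The set has been found feasible and reliable for adults with ID". The tests are done three times before PRET, so familiarity with them can build up within the baseline. The rule itself refers to understanding and not to the score; that a poor score would be read as poor understanding is an assumption. The article discloses both the dependence on instructions and the lack of blinding. An article may also leave to the full protocol how understanding is judged.

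Much of this stands. It limits the likely size, and it rules out a stronger reading that is tempting: that PRET trains the very skill on which recording depends, so that the fitness effect is biased. Section 2.4 says that participants learn the programme's own exercises, not the fitness tests, and nothing shows that different results will in fact be kept. The upward bias in Check 1 also needs more dropping at T3. Better understanding would not produce that; it would take a judgement swayed by the score.

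What the reply does not remove is the rule as stated. If entry screening made misunderstanding negligible, the rule would have nothing to do. Disclosing the lack of blinding as a measurement issue does not cover its role in deciding which results exist.

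**Conclusion.** The point holds in conditional form. The rule may select fitness results differently at T0–T2 and at T3, in a contrast with no control group. It could bias the fitness outcomes in either direction if the researcher's judgement is influenced by the observed score. If it follows understanding alone and understanding rises by T3, the bias is nil or slightly against PRET.

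Under the assumptions above the bias reaches about 0.08 SD at most, with false-positive rates up to 13% against a nominal 5% in the score-dependent scenarios. These figures illustrate what the rule could do and are not estimates for this trial, because the article gives no non-recording rates.

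The reach is limited. Fitness is a secondary outcome. Sarcopenia is affected only in part, since it also requires low muscle mass, which the rule does not govern. The primary cardiovascular outcomes are untouched. The case for acting is that the loss cannot be undone and the remedy is cheap.

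**What to change.** Replace the rule before measurements begin:

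1. Record every fitness attempt, with a yes/no 'understood' flag for each test. Set the flag by a fixed demonstration-and-practice step, before the scored attempt and before any score is seen.
2. Keep tests flagged as understood as the main analysis. This preserves the validity aim of the present rule. Do not make all attempts the main analysis, for the reason in Check 3.
3. Report the number flagged 'not understood' at each visit, so that a shift between T0–T2 and T3 is visible.
4. Add two sensitivity analyses: one with all attempts, and one restricted to participants flagged as understanding both at T0–T2 and at T3.

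The cost is one tick-box per test and a little more analysis work. The researcher will still know the visit, so the fixed criterion reduces the scope for a phase-dependent judgement without removing it. The counts and the stored attempts allow a reader to see how much it matters.
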